## Abstract

**Background:**

There are concerns over safety of older drivers due to increased crash involvement and vulnerability to injury. However, loss of driving privileges can dramatically reduce independence and quality of life for older members of the community. The aim of this trial is to examine the effectiveness of a safe transport program for drivers aged 75 years and older at reducing driving exposure but maintaining mobility.

**Methods and design:**

A randomised trial will be conducted, involving 380 drivers aged 75 years and older, resident in urban and semi-rural areas of North-West Sydney. The intervention is an education program based on the Knowledge Enhances Your Safety (KEYS) program, adapted for the Australian context. Driving experience will be measured objectively using an in-vehicle monitoring device which includes a global positioning system (GPS) to assess driving exposure and an accelerometer to detect rapid deceleration events. Participation will be assessed using the Keele Assessment of Participation (KAP). Data will be analysed on an intention-to-treat basis; the primary outcomes include driving exposure, rapid deceleration events and scores for KAP. Secondary outcomes include self-reported measures of driving, socialisation, uptake of alternative forms of transport, depressive symptoms and mood. A detailed process evaluation will be conducted, including examination of the delivery of the program and uptake of alternative forms of transport. A subgroup analysis is planned for drivers with reduced function as characterized by established cut-off scores on the Drivesafe assessment tool.

**Discussion:**

This randomised trial is powered to provide an objective assessment of the efficacy of an individually tailored education and alternative transportation program to promote safety of older drivers but maintain mobility. Trial registration: Australian New Zealand Clinical Trials Registry ACTRN12612000543886.

## Background

Older people are a large and growing sector of the driving population. Concerns over safety of older drivers have been raised due to increased crash involvement and vulnerability to crash injury [1-3]. Crash involvement per mile driven and likelihood for driver responsibility begins to increase from age 65 [4] and by age 85 likelihood of crash involvement is approximately 2.5 times higher than that of the younger drivers [5]. However, concerns over safety need to be tempered by the fact that driving is an important means to maintain independence and community participation for older people. Loss of driving privileges has been linked to depression and early admission to residential care [6].

Unlike younger drivers whose higher crash rate is attributed to inexperience and risky driving behaviour [4] the high crash rate for older drivers is explained by a different set of factors including visual, cognitive and functional decline, chronic conditions and medication. Compared with younger drivers, older drivers are over-involved in angle crashes, overtaking or merging crashes, and especially intersection crashes [4,7-9].

Driver licensing systems regulate driving privileges and most jurisdictions have restricted licenses for drivers with functional limitations. These are designed to keep less competent drivers in low-risk driving situations. Screening programs to evaluate functional status have been pilot tested in Australia [10] and proposed in the US [11]. However, recent reviews of available evidence find that there was no off-road screening test of fitness to drive that could be justified as a determinant of licensing status.[12,13] This was mainly due to concern about cost-effectiveness of screening all older drivers and limited effectiveness at identifying high risk drivers.

Self- regulation remains a central strategy for reducing crash risk amongst older drivers. Approximately 3-5%[14,15] of older drivers retire from driving each year and one quarter to one third make at least one adaptation to the way they drive.[16-18] Self-restriction and giving up driving has consistently been linked to decline in vision,[15,17,19-23] cognition [17,19,22,24,25], physical strength[24] and poor health [15,17,21,22,25,26]. Importantly, those drivers who self-regulate their driving have been shown to have poorer performance in on-road assessment.[18] An analysis of a case series of fatal crashes involving older drivers from the North American Fatality Analysis Rating System (FARS-2003) found that those who drive in the daylight were 28% (8 am-1 pm) and 37% (2 pm-8 pm) less likely to be injured in a crash [27]. Older drivers with a previous motor vehicle conviction, are 35% less likely to be injured in a crash presumably as these individuals acknowledge their limitations and take corrective action such as reducing their exposure to driving[27]. This epidemiologic evidence provides support for the use of self-restriction as a means to optimise the safety of older drivers.

While self-regulation is a promising tool to promote safety, external factors may over-ride considerations of driving ability and prevent an informed and timely decision [27]. It has been shown that a personal preference to be the driver (rather than a passenger) keeps drivers on the road [28]. The availability of alternate transportation[16] and another driver in the household [22] also increases the likelihood of stopping driving or limiting driving. Surveys find few current drivers have planned for retirement from driving [16].

We hypothesise that self-regulation can be optimised and propose to evaluate the effectiveness of an integrated program consisting of education about safe driving and alternative transportation, on driving exposure and safety. In recognition that loss of driving can negatively impact independent mobility, we will evaluate the impact on community participation and socialisation. Lastly, the cost-effectiveness of the program will be evaluated and provide important direction for policy makers and guide decisions about programs for older drivers to manage their driving and resource allocation to transportation schemes for older members of the community.

## Methods

The study is a randomised trial, designed in line with the CONSORT statement [29], involving 380 drivers. As the greatest population of older drivers in Australia is in outer suburbs and semi-rural areas [30], we will recruit licensed drivers’ aged 75 years and older, resident in two local government areas (LGA) on the suburban outskirts of Sydney, the Hills and Hornsby-Kuringai Shires. These areas were selected as they have greater than the national population median of seniors resident in the LGA (>17% aged 65 and over) and low availability of public transportation as defined by absent rail and irregular or no public bus services. Participants will be recruited through advertising in local media, seniors groups and through a mail-out to members of a motoring organisation in New South Wales (Figure 1).

**Figure 1 F1:**
[figure not shown]
Flow chart of participation in the randomized trial evaluating a safe transport program.

In late 2009 the investigators conducted a series of 3 focus groups with older drivers, who were members of a community-based seniors club in the Hills Shire. There was consensus that driving was essential to their independence, with participants citing lack of transport alternatives with no taxi service, sporadic private bus transport and strong personal preference for being able to continue driving. As reported elsewhere [16] few had planned for retirement from driving though loss of driving privileges was perceived as incompatible with continued living in this area. All participants felt there were significant safety issues for older drivers but that these issues were limited to only a few drivers, not well represented in the media and overestimated by the driving public. This consultation highlighted the importance of independent mobility and the need for objective data to inform policy in this area.

The study will be conducted in adherence with the Declaration of Helsinki and all participants will sign a record of informed consent. The study protocol has been approved by the University of Sydney Human Research Ethics Committee.

### Study procedures

Drivers interested in participating will be asked to contact the study centre by phone and complete a short interview to confirm eligibility. Participants are limited to residents of the Hills and Hornsby-Kuringai Shires so local transport services can be integrated into our intervention program. The program is only available in English and requires involvement of the participant in the education and planning so participants who do not have conversational English and those with evidence of a significant cognitive deficit will be excluded from the study [31]. As driving will be measured objectively, we require that participants are the primary driver of their own car and that they agree to have the in-vehicle monitoring device installed for a period of 12 months. The eligibility criteria are therefore; aged 75 years or older and resident in the Hills Shire, holder of a current drivers’ license, primary driver of their own vehicle, speak conversational English and two or less errors on the Short Portable Mental Status Questionnaire [31].

A baseline assessment will characterise the drivers enrolled in this study and will be conducted during a home visit lasting 1.5-2 h. Comorbidities [32], medication and alcohol use, presence of depressive symptoms (Geriatric Depression Scale [33]) and mood (Positive and Negative Affect Scale [34]) will be assessed by questionnaire. Driving relies heavily on cues from vision and we will assess vision using a measure of contrast sensitivity (Mars Perspectix letter chart) [35]. Contrast sensitivity appears to be a better predictor of driving performance than high contrast visual acuity. Owsley et al. [36] showed that contrast sensitivity was associated with crash involvement whereas visual acuity and glare sensitivity showed no significant associations. There are a number of measures of cognition relevant to driving abilities [37] and the Trail Making Test Part B is selected as it is portable, easy to administer, normative data are available [38] and it is predictive of driving performance [39]. The Trail Making Test Part B is a test of visual scanning and processing and executive function [40]. Longer times to complete the TMT Part B have been associated with poor driving performance in a number of studies [41-44].

Use of spectacles, problems with vision including cataracts and how recently they had an eye examination will be recorded. Visual attention implies the ability to pay attention to more than one object in the visual field and deficits in visual attention are related to driving errors [45,46] and crash risk [47] in older drivers. There are a number of assessments which evaluate visual attention however, we elected to administer the DriveSafe assessment tool as it assesses visual attention in a series of driving scenes and also considers awareness of functional limitations [48]. DriveSafe produces an overall score and has also been validated against on-road driving performance [49].

### Intervention

We propose to work with a group of older drivers to help them make informed choices about transport, thereby promoting safety but maintaining mobility and community engagement. Educational programs have been shown to increase use of safe driving strategies [51] and have included classroom modules [52], one-on-one counselling [53], video programs [54] and home based CD-rom or workbooks [6]. The KEYS program was selected as the basis for our intervention as it is well grounded in social-cognitive theories of behaviour [53]. While not proven to be protective against crash risk in a small trial in the US [55], Owsley demonstrated that the KEYS educational program, administered to a group of older drivers with visual acuity deficits or slowed visual speed of processing, increased self-reported safe driving practices [56].

The KEYS program has been adapted for the Australian setting and comprises two one-on-one sessions conducted in the participant’s home. The education is not ‘one size fits all’, instead it will be customised to meet the stage of behaviour change of the participant using the Precaution Adoption Process Model [57]. Understanding the stage of precaution adoption and self-regulation behaviour of each individual will allow the educator to tailor the approach and educational content. This targeted education aims to move participants through the stages of behaviour change towards adoption of safer driving practices [58].

The skill-building component raises the drivers’ awareness of their own skills and abilities and helps drivers match their driving skills to their driving exposure. The educator assists drivers translate this information into appropriate self-regulatory strategies that aim to promote safe driving for as long as possible. Finally, the intervention will build participant’s confidence in their ability to make changes to their driving habits. Strategies will include giving examples of other older drivers who have changed the way they drive and working with participants to set goals regarding changing their driving.

We know that lack of alternative transportation keeps older drivers on the road, independent of deficits in vision or cognition [16] and the need for alternate transport was reinforced in our community consultation. In the Hills district, in addition to limited bus routes, two types of community transportation services are available for seniors, firstly social outings in community buses and secondly door-to-door services. The latter run at subsidised cost (i.e., a volunteer gets paid per km to transport the user). The Australian Bureau of Statistics estimates that during a fortnight, those aged 75 and over primarily take trips for shopping (>80%), visiting relatives and friends (58%) but also medical appointments, church or other outings [30]. As part of the intervention delivered in this study, using an occupational therapy problem solving process [59], participants are encouraged to consider life without a licence and devise a plan for staying active, connected and independent within their community when they retire from driving. To formulate this plan, an inventory of desired trips will be taken and the participant counselled about alternatives to driving, utilising public transport, door to door community transport, and council community buses.

### Outcome assessment

#### Safety

A primary aim of this research will be to determine if driving safety is promoted through reduced driving exposure and fewer rapid deceleration events in the group participating in the program. An in-vehicle monitoring device or ‘black box’ will be installed into participants’ own vehicles by a mobile technician. The device consists of an in-vehicle data logger, three-axis accelerometer and GPS receiver, hard-wired to the vehicle which transmits time-stamped data on changes in speed and location every 20 s during vehicle operation. Data will be transferred weekly to a secure server and the devices will remain in the participants’ vehicle for 12 months.

The in-vehicle monitoring system has been validated in pilot study and laboratory experiments [60]. The device also has recently been field tested in 30 vehicles in metropolitan Sydney. Data quality was accurate and validation studies found 97% of trips were captured [61]. Importantly the device requires no involvement from the participant and in previous studies was well received by those involved. Rapid deceleration events will be defined as 500 m-G or higher deceleration [Meredith 2012]. Deceleration has been proposed as an indicator of a possible near–crash event [62]. and is a useful outcome measure when alternative outcomes such as crashes are infrequent and require large sample sizes. In-vehicle monitoring is an objective measure and all data will be processed by research assistants not involved in delivery of the intervention who will be blinded to treatment allocation. As the program is individualised, we hypothesise that the effect of the program will be greater in those participants with worse levels of function and this is a pre-specified sub-group analysis based on scores on the DriveSafe/DriveAware assessment {Kay, 2009 #2230} [48].

Secondary outcome measures of driving exposure include night driving and radius of travel from home. These variables will also be constructed from data collected by the in-vehicle monitoring system. Self-reported driving habits will be used as secondary outcome measures and survey responses compared at the 12-month time-point, adjusting for baseline. We will use an adapted version of the Driving Habits Questionnaire (DHQ) [63] and instruments developed for Australian populations by Baldock et al. [9] and Sullivan et al. [64] to assess self-reported driving habits, confidence in driving and self-reported avoidance of particular driving conditions. Other secondary outcomes include presence of depressive symptoms [65] and mood [34].

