### Sample size and statistical analysis

Previous research has found that approximately 12% of older drivers report crash involvement during a 12-month period [67]. However, near misses are approximately 18 times higher than crash rates [68]. We may therefore expect to document approximately 370 incidents (crashes and near misses) during our period of observation (rate 0.73 per person/year)[68]. With a 5% level of significance and 80% power, we require 178 in each arm to detect a 20% reduction in combined crash and near miss rates (i.e., IRR=0.80). Allowing for drop-outs rate of 5%, we will enroll 380 into the program (190 in each arm). We will be able to measure a difference of 6 km in daily distance travelled (~30% reduction), using daily mileage in a population of older drivers [28]. Differences in the Keele Assessment of Participation will also be well served by this sample size.

An intention-to-treat approach will be used for all analyses. Driving exposure (kilometres travelled) and the number of rapid deceleration events (RDE) during 12 months will be compared between the intervention and control groups. A linear regression model will be used to compare the groups with weeks of driving as a covariate. Mobility and community participation will also be compared between the two groups using a similar analytic approach. A subgroup analysis will be performed on each primary outcome defined by the cut-off on DriveSafe/DriveAware [1], for needing further assessment (95 and below). As the primary analysis is based on multiple endpoints (3), the results will be interpreted with caution if the statistical significance is borderline (i.e., a *p*-value between 1.66% and 5%) due to multiplicity issues. Continuous secondary outcomes will be analysed using linear regression models with generalized estimating equations for repeated measures (e.g., weekly radius from home) and count data analysed using Poisson or negative binomial regression models as appropriate. Analyses will be conducted using the SAS and STATA software packages.

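### Weeks of driving, the only time adjustment stated for the two device outcomes, does not separate true non-driving from a failed device or a replaced car

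*Protocol article*

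**What the plan says.** All references are to the protocol article.

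- **Outcome assessment, Safety.** The logger "will be installed into participants’ own vehicles by a mobile technician", is wired into that one car, and is described as a device "which transmits time-stamped data on changes in speed and location every 20 s during vehicle operation". On transfer and duration: "Data will be transferred weekly to a secure server and the devices will remain in the participants’ vehicle for 12 months". On completeness: "validation studies found 97% of trips were captured". The aim is to find out whether "driving safety is promoted through reduced driving exposure and fewer rapid deceleration events". No idle or status signal, fault log, date of stopping driving or procedure for a changed car is described.
- **Sample size and statistical analysis.** "Driving exposure (kilometres travelled) and the number of rapid deceleration events (RDE) during 12 months will be compared" between the arms, and then: "A linear regression model will be used to compare the groups with weeks of driving as a covariate". The article does not say whether this covariate counts weeks in which the device worked or weeks in which the participant drove.
- **Background.** Some 3-5% "of older drivers retire from driving each year".
- **Intervention and Discussion.** Planning for life after driving is part of the programme, and helping people retire from driving in good time is named as a use of it.

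**The concern.** A week with no data has at least two possible meanings. The participant may not have driven, which is a real 0 km and 0 RDE and, in the intervention arm, may be the programme working. Or the device may have failed, or the car may have been sold and replaced, in which case the week was not observed. The right handling is opposite in the two cases: the first belongs in the 12-month total as zero, the second should be taken out of follow-up time.

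The stated covariate, read literally, makes no such distinction. A participant who stops at week 26 and one whose device dies at week 26 both have 26 weeks of driving. Adjusting for that number suits the second person. For the first, it conditions on something the programme may have changed and removes that part of the effect. Two primary outcomes are exposed, and the facts needed to sort silent weeks may be lost if they are not collected during the trial.

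**Working it through.** **Inputs from the document.** A detectable difference of 6 km/day, described as about a 30% reduction; 178 analysed and 190 enrolled per arm; 5% significance (taken as two-sided) and 80% power; a planned 20% reduction in the joint rate of crashes and near misses; 3-5% yearly retirement from driving.

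**Inputs assumed.** Rates of device failure, car replacement and extra stopping due to the programme. The document gives none, so ranges are shown.

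**Step 1. Plan's own figures.**
- Implied mean driving: 6 / 0.30 = 20 km/day.
- SD implied by 6 km at 178 per arm: 6 / [(1.960 + 0.842) × √(2/178)] = 20.2 km/day.
- The 178 itself comes back as 179 if 0.73 and 0.584 are treated as proportions with a continuity correction. A two-sided comparison of Poisson rates gives 482-486. That is a separate matter; here 178 serves only to obtain the SD and to set the arm size in step 4.

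**Step 2. What stopping contributes to the arm difference.** If an extra share *s* of intervention drivers stop at mid-year, the difference is 20 × *s* × 0.5:
- 3%: 0.3 km/day, 5% of the 6 km target
- 5%: 0.5 km/day, 8%
- 10%: 1.0 km/day, 17%

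This is the amount at risk if silent weeks are adjusted away. For scale, 3-5% of 190 is about 6 to 10 people per arm. That is the background rate, not an estimate of the programme's effect.

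**Step 3. What unequal faults contribute.** If fault weeks are coded as zero, each percentage point of imbalance between arms gives a false 20 × 0.01 = 0.2 km/day. A 5-point imbalance gives 1.0 km/day, and a false 5% fall in RDE, a quarter of the planned 20%.

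**Step 4. Simulation of the stated model.** 2,000 trials of 178 per arm; mean 20 and SD 20.2 km/day; silence starting at a uniformly random time in 52 weeks; weeks of driving taken as weeks with device data. No change in weekly distance is built in for those who keep driving, so only stopping and failure are at work. Percentages are intervention v control; differences are in km/day.

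| Case | Stopping | Failure | True difference | Silence coded zero | Adjusted for weeks |
|---|---|---|---|---|---|
| A | 30% v 4% | none | -2.60 | -2.60 | -0.01 |
| B | 4% v 4% | 26% v 0% | -0.02 | -2.55 | -0.03 |
| C | 20% v 4% | 5% v 5% | -1.55 | -1.50 | +0.05 |
| D | 10% v 4% | 5% v 5% | -0.60 | -0.58 | +0.01 |

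Hand check of A: 20 × (0.30 - 0.04) × 0.5 = 2.6. Monte Carlo error is about 20.2 × √(2/178) / √2000 = 0.05.

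**Reading.** A and B have almost the same pattern of silence and opposite truths. Coding zero is right in A and wrong in B; adjusting is right in B and wrong in A. In C and D, with equal faults, coding zero is nearly unbiased, while the adjustment still removes the whole stopping effect.

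**The case against.** **A condensed article may leave gap rules to a fuller document.** This stands as far as it goes: the absence of a missing-data rule alone would be no finding. But the article does state an adjustment, and that adjustment, followed as written, can remove a real effect. An analysis plan written later also cannot supply facts that were never recorded.

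**A reader might infer that the trial cannot tell zero from missing.** The document does not support that. A weekly transfer that continues without trips might show a live device, though the article does not say so. GPS positions could screen gaps that are followed by another trip. Self-reported driving habits (Safety) and driven trips reported at the 12-month visit (Mobility) might identify people who stopped. The supported statement is that nothing stated links these to the device outcomes.

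**The covariate is undefined and may already mean weeks of working device.** It may. If so, the remedy is mostly one of wording, plus the data to support it.

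**A reader might infer that every way of handling silence is biased.** Cases C and D show otherwise for balanced faults coded as zero. Case B needs a failure imbalance of 26% v 0%, for which the document offers no mechanism: the device needs nothing from the participant, and blinded staff process the data.

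**A reader might take the 97% trip capture to exclude outages.** The article does not say either way. It is a validation result, not stated as uptime over 12 months.

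**The large loss in case A comes from a post-randomisation covariate.** True, and adjusting for such a variable is open to question in its own right. But removing it does not settle how silent weeks enter the totals; they must still be classified.

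**Conclusion.** The point holds in a limited form. Nothing stated separates true non-driving from a failed device or replaced car, and the one stated time adjustment, read literally, treats them alike and can remove the effect of stopping. Stopping is one route to the intended reduction, not the only one; shorter or fewer trips by people who still drive each week are not lost in this way.

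The size rests on assumptions. At 3-5% excess stopping from mid-year it is about 0.3-0.5 km/day, small against 6 km. It is also small with balanced faults coded as zero. It reaches about 2.6 km/day only under large contrasts such as 30% v 4% stopping, or 26% v 0% failure coded as zero, and these are illustrations, not forecasts. The change is worth making because it is cheap, it protects two primary outcomes, and for sold cars and failed devices the information may not be recoverable afterwards.

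**What to change.** 1. **Analysis.** Replace weeks of driving with weeks of working-device observation as follow-up time. Keep verified non-driving weeks as observed, with 0 km and 0 RDE. Treat device failure or a changed car as unobserved time.
2. **Data.** Record the odometer at device installation, at removal and at any change of car. At the existing 12-month visit, ask for the date last driven and about any change of car.
3. **Gaps.** Use GPS continuity (does the next trip start where the last one ended?) only as a screen. Missed round trips from home pass that test, so it cannot prove non-driving. Where the odometer shows distance that the device missed, correct kilometres from the odometer and treat the gap as unobserved for RDE, because an odometer cannot recover events.

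**Cost.** Some coding work, a few odometer readings and two questions. Odometer data, like the device data, belong to the car and not the driver. The article states a technician visit for installation only; one at removal is assumed here.
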